#### Parents

Consenting parent participants will: i) be the parent of a child 0–5 years (inclusive); ii) be recommended to participate in the program by an early childhood practitioner working at a participating pilot site; iii) aged 18 years and over; iv) currently reside in the state of Victoria or New South Wales, Australia; and v) feel comfortable completing questionnaires and program materials in English.

### Sample size/power calculation

Power analysis was conducted using the G*Power 3.1 software to determine the required sample size for this study [34]. A single group within study design would require 199 parent participants to identify a small to moderate statistically significant effect (.20) at *p* < .05, with 80% power. To account for parent participant attrition, we aim to recruit approximately 480 parents.

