### Design

MERTIL *for Parents* will be examined via a parallel armed (i.e., practitioners and parents), uncontrolled, mixed methods, repeated measures study design. Practitioners will complete two assessments (pre-parent recruitment and three-month post-program) and parents will complete three assessments (pre-program, program exit, and three-month program follow-up). All practitioners and parent data collection and completion will be conducted independently and in parallel.

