#### Sample

We aim to recruit 48 practitioners, consisting of 24 MCH practitioners from Universal MCH services, and 24 MCH practitioners from high-risk Enhanced services. These practitioners will in turn recruit the above-mentioned 480 parents.

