### Data analysis strategy

#### Quantitative

All statistical analyses will be conducted using the software IBM SPSS Statistics [45]. Descriptive statistics will be generated to identify professional and parent population characteristics and to evaluate parent and professional program perceptions. To determine parenting change in dyadic attachment, relational function, maternal mental health, from pre-program to three-months post-program, inferential statistics will be used (i.e., univariate, bivariate, and multivariate analyses) such as t-tests, chi-squared analyses, ANOVA, and regression analyses.

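### The sample size of 199 assumes independent parents and the rise to 480 is assigned to attrition alone, although parents are nested within 48 referring practitioners

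*Protocol article*

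**What the plan says.** The section Sample size/power calculation gives the basis: "A single group within study design would require 199 parent participants to identify a small to moderate statistically significant effect (.20". The significance level there is 5% and the power 80%. The step from that figure to the target has one stated reason: "To account for parent participant attrition, we aim to recruit approximately 480 parents". No attrition rate is given.

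The Sample section sets 48 practitioners, 24 from Universal and 24 from Enhanced services, and adds: "These practitioners will in turn recruit the above-mentioned 480 parents". Under Eligibility criteria a parent can enter only on a practitioner's recommendation, and the practitioner must be able to contact each referred parent afterwards. Procedure places that contact within two weeks of the recommendation. Recruitment of study populations places the practitioners in four metropolitan and four regional or rural LGAs.

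For change from pre-program to three months, the Quantitative part of Data analysis strategy names methods "such as t-tests, chi-squared analyses, ANOVA, and regression analyses". The article mentions no ICC, design effect or practitioner-level term.

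**The concern.** Parents who share a practitioner share how the program was introduced, the follow-up contact, the service stream and often the locality. The follow-up contact comes before the three-month outcome, so it can affect change as well as the starting level. If change is correlated within practitioner, 199 parents carry less information than 199 independent ones. A test that ignores this has standard errors that are too small, confidence intervals that are too narrow and a false-positive rate above 5%.

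The sample-size basis is stated in the article, not deferred, and it does not match the recruitment scheme in the section that follows it. The whole surplus from 199 to 480 is assigned to attrition, so none of it is set aside for clustering. The same surplus cannot be spent in full on both.

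**Working it through.** **Inputs from the article.** Effect .20, read as the standardised mean of the paired difference (the metric is not named); alpha .05 (sidedness not stated); power 80%; 48 practitioners; target 480.

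**Reproducing 199.** For an exact paired t-test (noncentral t), two-sided .05 and effect .20, n = 199 gives power .8017 and n = 198 gives .7997. A one-sided test would need only 156. So 199 is the two-sided figure for independent parents and contains no clustering allowance.

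**Implied attrition and cluster size.** 1 − 199/480 = 58.5%. Parents per practitioner: 480/48 = 10 recruited, or 199/48 = 4.15 if only 199 are analysed.

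**Assumption.** The article gives no ICC for the change score. The range .01 to .10 is assumed, with equal numbers of parents per practitioner.

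**Formulas.**
- Design effect: DE = 1 + (m − 1) × ICC, with m = n/48.
- Effective sample size: n/DE. Power is taken from the noncentral t at that size.
- True alpha of an unadjusted test: 2 × (1 − Φ(1.96/√DE)).
- Analysed parents for 80% power: solve n/DE = 199 with m = n/48, which gives n = 199 × (1 − ICC)/(1 − 199 × ICC/48).

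Example at ICC .10: DE at 199 is 1 + 3.15 × .10 = 1.31. The requirement is 199 × .90/(1 − .4146) = 179.1/.5854 = 306. Attrition affordable from 480 is 1 − 306/480 = 36%.

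| Assumed ICC of change | .01 | .02 | .05 | .10 |
|---|---|---|---|---|
| DE, 199 analysed | 1.03 | 1.06 | 1.16 | 1.31 |
| Power, 199 analysed | 78.9% | 77.7% | 74.1% | 68.6% |
| Unadjusted alpha, 199 analysed | .054 | .057 | .068 | .087 |
| Analysed parents for 80% power | 206 | 213 | 239 | 306 |
| Attrition from 480 that still leaves 80% power | 57% | 56% | 50% | 36% |
| DE, 480 analysed | 1.09 | 1.18 | 1.45 | 1.90 |
| Power, 480 analysed | 98.7% | 98.1% | 95.2% | 88.6% |
| Unadjusted alpha, 480 analysed | .060 | .071 | .104 | .155 |

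**Intermediate attrition, same ICC order.** With 336 analysed (30% lost), power is 94, 93, 89 and 82%. With 240 analysed (50% lost), it is 86, 84, 80 and 74%.

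**Limits of the figures.** Using 47 degrees of freedom for 48 practitioners, in place of n/DE − 1, lowers the power at 199 by a further 1.2 to 1.3 points. Unequal caseloads would raise the design effect.

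**The case against.** The strongest reply is that the result turns on an ICC of within-parent change that no document supplies, and that it may be small. Stable differences between practitioners' caseloads cancel in a pre-post difference. The program is self-directed, online and the same for everyone, and the practitioner's later role is one informal contact. At ICC .01 to .02, even with only 199 analysed, power is 78 to 79% and unadjusted alpha .054 to .057. This stands, and it makes the low end of the range plausible. It does not remove the point, because differences in change between service streams, or arising from the practitioner's follow-up, do not cancel.

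The second reply is that 480, not 199, will be recruited. This also stands for power: at 30% attrition, power stays above 80% across the whole assumed range. It does not help the error rate, because more parents per practitioner make an unadjusted test more anti-conservative.

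The third reply is that the list of tests is illustrative and includes regression, and that a fuller protocol or analysis plan may handle clustering. This is fair, so the alpha figures apply only if the tests are run unadjusted. The sample-size statement is not open in that way.

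Three stronger readings may tempt a reader:
- That the trial fails to deliver 80% power and a 5% error rate. The article does not support this as a fact: power falls short only if attrition uses up most of the surplus, and alpha is inflated only without adjustment.
- That the requirement is 199 times the design effect at 4.15 parents per practitioner, which gives 262 at ICC .10. With 48 practitioners fixed, cluster size grows with n. At 262, m = 5.46, DE = 1.446 and power is about 76%.
- That the Design section's remark about independent and parallel data collection assumes statistically independent parents. It describes the separate practitioner and parent data streams.

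**Conclusion.** The point holds in a limited form. The 199 makes no allowance for clustering by practitioner, and neither does the reason given for 480. For any positive ICC of change, the number of analysed parents needed exceeds 199: about 206 to 306 over the assumed range. The tolerable attrition falls from the implied 58.5% to between about 57% and 36%. The target of 480 is probably adequate, but the article does not show it, and its own limitations section warns that attrition may be high.

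The more lasting issue is the analysis. Over the same range, unadjusted tests would have a true alpha of about .054 to .087 with 199 analysed and .060 to .155 with 480. All these figures rest on the assumed ICC and equal caseloads. The study is an uncontrolled pilot that disclaims causal inference, which limits the stakes. The change is still worth making because it costs so little.

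**What to change.** - Restate the requirement with an assumed ICC of change and an attrition rate, both given as numbers, and show that 480 covers the two together. Compute it with 48 practitioners fixed, so that cluster size rises with n.
- Record the referring practitioner for each parent at registration, if this is not already captured; a practitioner code on the referral flyer would do. It should be in place before recruitment, because the link may not be recoverable later.
- Analyse change from pre-program to three months with a practitioner random intercept or with practitioner-clustered standard errors.
- Fixed effects for service stream or region are optional. Clustering by LGA, with only eight areas, belongs in a sensitivity analysis.

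The cost is a restated paragraph, one extra recorded field, a different analysis procedure and slightly wider confidence intervals. No additional parents are needed.

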#### Sample

We aim to recruit 48 practitioners, consisting of 24 MCH practitioners from Universal MCH services, and 24 MCH practitioners from high-risk Enhanced services. These practitioners will in turn recruit the above-mentioned 480 parents.

### Recruitment of study populations

#### Practitioners

The authors will recruit through their existing MERTIL *for Practitioners* MCH nurse and perinatal mental health networks, ensuring a representative sample of MCH nurses and specialist perinatal and infant mental health clinicians from differing Australian geographic locations. Participating sites will include four Victorian and New South Wales metropolitan LGAs and four Victorian and New South Wales regional/rural LGAs, based on pre-existing profession networks. To further ensure representativeness, recruitment will include healthcare practitioners from the Universal and Enhanced MCH services, and from specialist perinatal and infant mental health clinics. All participating practitioners will provide online consent to their study participation.

#### Parents

Parents who meet inclusion criteria will be informed about the study by their MCH practitioner during a visit to a Universal MCH service (any of the scheduled visits from the initial post-birth home visit, consultations at 2, 4, & 8 weeks; 4, 8, 12, & 18 months; 2 & 3.5 years), or from any Enhanced MCH service engagement (i.e., MCH centre or specialist perinatal and infant mental health clinics). The practitioners will explain MERTIL *for Parents* and the associated research project, and if the parent verbally expresses interest, practitioners will direct them to the MERTIL *for Parents* website to register for the study and to access the materials (www.mertil.com.au). Practitioners will provide parents with a printed flyer with MERTIL *for Parents* details to aid this process. For parents who verbally agree to participate, practitioners will follow-up to gauge parents’ program responses.

During the study pilot phase, parents recommended to the program will go to the MERTIL *for Parents* website to join the research. Specifically, parents will be met with a webpage popup with a brief research overview and the option to hear more about the study. If parents select to hear more about the research, they will then be automatically prompted to enter their first name and email address. This will trigger access to an explanatory statement of the study and the option to consent to the research. Once the completed forms are submitted, parents will be invited to participate in a brief 10-minute pre-program baseline survey. Completing this survey will grant parents access to the MERTIL *for Parents* program.

### Procedure

#### Practitioners

Following informed consent, practitioners will attend a 120-minute web-based information and training session on MERTIL *for Parents*. This session will provide a study overview to promote program and pilot study familiarisation. Immediately following this session, practitioners will be asked to complete an online survey to report their first impressions of MERTIL *for Parents* regarding factors such as perceived program content, length, and suitability.

Practitioners will be asked to make contact with parents they refer to the program, within two weeks of recommending MERTIL *for Parents*. This follow-up contact will be via an informal face-to-face chat, phone call, or email. Once practitioners have recommended the program to parents, they will be invited to complete a second survey. This final practitioner survey will assess views on program usability, impactfulness, engagement, and ideas for program refinement and wider implementation. Online focus group interviews will follow to elaborate on survey responses, assess practitioner views and experiences of the program, potential barriers to implementation, and to identify further uses and applications of MERTIL *for Parents*. These elements will ensure MERTIL *for Parents’* co-designed nature endures. See Fig 4 for the professional data collection flow diagram.

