## Methods

### Study aims

This paper reports on a protocol for the pilot implementation of a new self-directed, universal, online parenting program, MERTIL *for Parents* (My Early Trust-Informed Learning), within the Maternal and Child Health (MCH) sector. The aims of this study are twofold:

Determine the feasibility of MERTIL *for Parents*:
For practitioners: Examine the programs acceptability and utility for enhancing parent understanding of early relational health; assess the practical dimension of implementing the program within a busy service; and explore population reach.For parents: Examine program acceptability and utility.Evaluate the short-term efficacy of MERTIL *for Parents* across selected parental caregiver knowledge, perceptions (e.g., parenting confidence and competence), and behavioural domains (e.g., professional help-seeking amenability).

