### Eligibility criteria

#### Practitioners

To be eligible for study participation, practitioners will: i) have completed MERTIL *for Practitioners*, ii) work at a participating Australian pilot site, in metropolitan or regional/rural Victorian and New South Wales, and iii) be able to make a follow-up contact (via a phone call, email, or face-to-face chat) to each of the parents they refer to the program, to gather feedback.

For practitioner participants, two key programs sit within the MCH umbrella: i) Universal services, and ii) Enhanced services [29]. Participants will be comprised of Universal and Enhanced service practitioners. Universal services are available to all families, while Enhanced services support ‘at-risk’ families. Universal practitioners will comprise of mostly MCH nurses from MCH centres, while Enhanced practitioners will include clinical staff from MCH centres *and* perinatal and infant mental health clinics. Enhanced service staff will include not only MCH nurses, but also psychologists, social workers, and psychotherapists. Study participation invitations will further be sent to practitioners who work in both the Universal *and* Enhanced services.

For practitioners who decide to participate, free access to MERTIL *for Practitioners* will be provided for the duration of the pilot study. All practitioners will have already completed this training; however, ongoing access will allow practitioners to refresh their knowledge of and skills in identifying early relational trauma, if necessary. Practitioners will also have ongoing access to MERTIL *for Parents*.

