#### Practitioners

After practitioners hear from the parents they recommended MERTIL *for Parents* to, practitioners will be asked to complete a brief mixed methods online survey, allowing insight into practitioners’ perceptions of the program. Questions will include: i) *Would you recommend MERTIL for Parents to future parents*? ii) *Would you recommend colleagues encourage future parents to participate in MERTIL for Parents*? iii) *From your perspective*, *does MERTIL for Parents fill a current preventative health gap*? and iv) *Are there any existing gaps in the MERTIL for Parents program*? For each question response, options will be ‘yes’ or ‘no’, and then practitioner participants will be asked to expand upon their answer with free text.

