## Discussion

### Limitations and challenges

While this study is innovative, we foresee several program content and delivery method limitations: Firstly, it is possible that the brief self-guided content of MERTIL *for Parents* may not provide adequate content information and support (i.e., program dose too low). Second, as frontline services, practitioners may lack the time in session to explain and recommend parents to participate in MERTIL *for Parents*, due to competing demands and scheduling pressures. Third, as the study population pertains only to practitioners and parents located in Victoria and New South Wales, Australia, generalisability concerns will be present for interstate Australian and international populations. Fourth, as all MERTIL *for Parents* content is housed online, this may exclude those who lack the technology or skills to participate, especially as on-demand technical support will not be available for live participant trouble shooting. Further, because of this study’s non-randomised sampling strategy, cause-effect relationships cannot be drawn. That is, parents’ socioemotional outcome changes cannot be causally inferred by their MERTIL *for Parents* participation. Finally, as with all research, there is a risk that attrition rates may be high. All parent data will be self-report in nature, and interpretation of findings will therefore be subject to these limitations.

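### The final practitioner survey is described as following a recommendation and parent feedback, so practitioners who recommended to nobody may be missed and the practitioner feasibility results are likely to be too favourable

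*Protocol article*

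**What the plan says.** The protocol article describes the timing of the second practitioner survey in three ways.

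- **Procedure, Practitioners:** "Once practitioners have recommended the program to parents, they will be invited to complete a second survey". The section calls this the final practitioner survey. It covers usability, impact, engagement, refinement and wider implementation.
- **Measures, Practitioners:** the description begins "After practitioners hear from the parents they recommended" the program to, and continues: "practitioners will be asked to complete a brief mixed methods online survey, allowing insight into practitioners’ perceptions of the program".
- **Design:** "Practitioners will complete two assessments (pre-parent recruitment and three-month post-program", with no mention of having referred anyone. The Abstract likewise lists two practitioner data collection periods without a referral condition.

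The practitioner part of the feasibility aim (Study aims) includes to "assess the practical dimension of implementing the program within a busy service; and explore population reach". Limitations and challenges foresees that "practitioners may lack the time in session to explain and recommend parents to participate".

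Two other practitioner data sources are described. The first survey comes straight after the training session and records first impressions. Two practitioner focus groups of 4–6 optional volunteers follow, and implementation barriers are among their topics. The Sample section plans 48 practitioners and 480 parents.

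**The concern.** A practitioner who enrols, finds no time in consultations and recommends the program to nobody is an implementation failure, and the feasibility aim exists to detect such failures. Under the Procedure and Measures wording, that same event takes the practitioner out of the invitation to the only survey held after implementation. Under the Measures wording, so does recommending the program and hearing nothing back. Inclusion then depends on the outcome being studied.

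At stake is how the practitioner feasibility results can be read. If they come only from practitioners who managed at least one recommendation, they describe feasibility among those who could implement the program. They would be presented as feasibility in the services that took part. The conclusions are meant to guide program refinement and wider implementation, where the reasons for not recommending are among the most useful things to learn.

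**Working it through.** **1. The plan's own figures.** The article gives no sample size or precision figure for practitioners, so there is nothing to reproduce on this point. Its one calculated figure, 199 parents, does reproduce: a paired t-test with standardised effect 0.20 and two-sided 5% level gives n = 199 and power 0.802. It plays no part here.

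**2. Which source reaches a practitioner who recommended to nobody?**

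| Source | Reaches them? | Informs on implementation? |
|---|---|---|
| First survey (Procedure) | Yes | No: it precedes any implementation |
| Final survey, Procedure wording | Not provided for | Yes |
| Final survey, Measures wording | Not provided for; nor for those who heard from no parent | Yes |
| Second assessment, Design wording | Yes, if read as unconditional | Yes |
| Focus groups | Possibly: no referral condition is stated, but they are volunteers and the groups are to elaborate on survey responses | Yes, barriers are a topic |
| Parent surveys and website usage | No: they come from referred parents | Not on why a practitioner referred nobody |

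The focus groups hold 2 × 4 = 8 to 2 × 6 = 12 practitioners, that is 8/48 = 17% to 12/48 = 25% of those planned.

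The Design wording does not settle the matter. Three months post-program has no stated starting point for a practitioner with no referred parents.

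**3. Illustration of the selection effect.** Let k be the number of the 48 practitioners not reached, y the favourable proportion among those surveyed, and u the favourable proportion among those not reached. Then

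- proportion over all 48 = [(48 − k)·y + k·u] / 48
- overstatement = (k/48)·(y − u)

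None of k, y or u is in the documents. I assume y = 90% and take u = 0% and u = 30%.

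| k | Surveyed | Reported | All 48, u = 0% | All 48, u = 30% |
|---|---|---|---|---|
| 0 | 48 | 90% | 90% | 90% |
| 5 | 43 | 90% | 38.7/48 = 81% | 40.2/48 = 84% |
| 12 | 36 | 90% | 32.4/48 = 68% | 36.0/48 = 75% |
| 24 | 24 | 90% | 21.6/48 = 45% | 28.8/48 = 60% |

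The reported figure is 90% in every row. The gap vanishes if k = 0, or if those not reached would answer as favourably as the rest (u = y).

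**The case against.** The strongest reply is that the Procedure and Measures sentences describe the expected sequence and are not exclusion rules. Nowhere does the article say that a practitioner without referrals will not be invited. The Design section gives two assessments without condition, the practitioner flow diagram (Fig 4) is not visible here, and the article condenses a fuller protocol. This stands in part: exclusion follows from the wording but is not stated. It does not remove the point, because the two sections that describe how the survey is issued both tie it to referral, and no section gives a route or a question for those who refer nobody.

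A reader might infer that practitioners who could not fit the program in never report, and that feasibility is judged only by those for whom it worked. The documents do not support that. Every trained practitioner is asked for the first survey. One recommendation meets the Procedure condition, against a planned average of 480/48 = 10 parents each, so practitioners with partial difficulty or unfavourable feedback do report. The final survey asks about gaps in the program, with free text.

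A reader might also infer that the third eligibility criterion, that practitioners "be able to make a follow-up contact" with each parent they refer, screens out the same barrier. It does not. It concerns later contact with parents already referred, whereas the foreseen barrier is time in the session to explain and recommend.

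Two further replies have force. Practitioners who never used the program have little basis for rating its usability. And the yes/no items quoted in Measures ask for endorsement, which a practitioner too busy to refer might still give. The upward bias is therefore better founded for practicality of implementation than for those items.

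**Conclusion.** The point holds in a limited form. The article gives three different timings for the final practitioner survey, and two of them tie it to having recommended the program or heard back from parents. If those two are followed, practitioners who recommended to nobody or heard from no parent may be missed, and the practitioner feasibility results are likely to be too favourable. The first survey comes too early to fill the gap, and the focus groups fill it only in part.

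The size cannot be derived from the documents. It depends on how many practitioners are not reached and on how differently they would have answered, and it is nil if every practitioner recommends and hears back. The percentages in the table rest on assumed values and are not estimates of the bias. Feasibility is a secondary outcome under Measures, so this is a change that should be made but does not undermine the study's primary outcome.

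**What to change.** Reconcile Design, Procedure and Measures with one rule:

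- Send the final survey to all enrolled practitioners at a fixed time, whatever their referrals and whether or not parents responded. Count from a date that every practitioner has, such as the training session.
- Add two items: the number of parents recommended, and the main reason if few or none.
- Report the number who recommended to nobody, and the feasibility results over all enrolled practitioners. Show the usability items also among those who used the program.

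Leave the third eligibility criterion as it is.

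The cost is protocol wording and two survey items. There are small downsides: some respondents will have little experience of the program, and the feasibility figure may look less favourable.
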